*Functional activation: reward anticipation:* Most neurological models of addiction stress the importance of the mesocorticolimbic pathways in processing the reinforcing effects of drugs (Koob & Volkow, 2009). Drugs of addiction such as nicotine alter the sensitivity of the brain regions involved in motivation and reward (Robinson & Berridge, 2001). Many studies have shown that addicted individuals show blunted activations in response to non-drug rewards in these brain regions (Balodis & Potenza, 2015; Sweitzer et al., 2015). As a result, addicted individuals with impaired reward processing pathways may contribute to drug-seeking behaviors. Specific brain areas that could be responsible for these changes include: the ventral striatum (Peters et al., 2011), the nucleus accumbens (NAc) (Buhler et al, 2010, Sweitzers et al., 2015) and the anterior cingulate cortex (ACC) (Fedota et al., 2015). Specifically, previous studies have shown that individuals with lower ventral striatal activity during the reward anticipation task were more likely to smoke/relapse (Sweitzer et al., 2015). Another area of interest for nicotine addiction is the medial prefrontal cortex (MPFC), which contributes to goal-directed behaviours in response to reward expectation (Goldstein & Volkow, 2002). Lastly, varenicline has been previously implicated in the reduction of reward signaling and decreasing alcohol intake in humans and rodents (Franklin et al., 2011; Hendrickson et al., 2010). In a recent study, varenicline downregulated gain magnitude processing in the anterior cingulate cortex (ACC), an area associated with attentional control (Fedota et al, 2015). Specifically, varenicline decreased the impact of reward magnitude on ACC activity whereas nicotine increased ACC processing when anticipating a reward (Fedota et al., 2015). Thus, we will be examining differences in the above brain regions at baseline and comparing them with end of treatment scans. The sham tDCS group will allow us to examine the effects 12-weeks of varenicline treatment on reward anticipation in both quitters and non-quitters. Meanwhile, the active tDCS group will allow us to examine the effects of tDCS on reward anticipation compared to non-active tDCS.

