**Hypotheses**:

1. The combination of varenicline treatment plus tDCS to the left DLPFC will improve smoking cessation outcomes and relapse rates in treatment seeking smokers.
2. Active tDCS will reduce fMRI BOLD response to smoking cues compared to baseline within-subjects and compared to sham tDCS between subjects. Those who quit smoking in the last 4 weeks of treatment will show a “normalization” of brain reactivity to smoking cues and reward anticipation relative to those who were unable to remain abstinent over the short term due to tDCS extinguishing the salient properties of smoking-related cues and reward anticipation.
3. Compared to baseline, varenicline treatment will reduce within subject attentional bias, as measured by parameters of visual scanning behavior (VSB), to smoking and negative emotional cues.
4. Active tDCS will reduce attentional bias to smoking and negative emotional cues compared to sham tDCS. Those who quit smoking in the last 4 weeks of treatment will show “normalized” attentional bias patterns to smoking cues and reward anticipation relative to those who were unable to remain abstinent over the short term. Subjective measures of cravings will be correlated with within-subject changes in attentional bias to smoking cues and reward anticipation.
5. Individuals with larger changes in attentional bias to smoking-related cues and/or negative emotional cues, and lower measures of attentional bias to high-arousal/high-risk cues will have higher rates of abstinence (less relapse). Attentional bias will be measured by parameters of visual scanning behaviour and through the analysis of visual scanning patterns (sequences of fixations).
6. The probability of remaining abstinent over the long term will be inversely correlated with VSB measures of novelty seeking behavior.
7. Active tDCS will reduce impulsivity compared to sham tDCS as measured by higher delayed discounting scores.

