**METHODS**

**Design**

This will be a double-blind sham-controlled two-arm randomized clinical trial. Fifty participants will be randomized (1:1) to each arm. Arm 1 will be active tDCS plus varenicline (n=25) and Arm 2 will be sham tDCS plus varenicline (n=25). Treatment duration will be 12 weeks. Subjects will be required to attend an in person assessment visit. They will then be randomized to a condition. Neuroimaging scans (fMRI) and eye-tracking tests will be conducted in all participants at baseline. Participants will undergo two scans at baseline on different days within the same week: one in a satiated state and one in a non-satiated state. The same tasks will be performed at each scan. s. Following the baseline fMRI scans and eye-tracking tests, subjects will start taking the varenicline simultaneous with starting the tDCS regimen whereby they will come to the clinic every day (Monday to Friday) for the first 2 weeks to undergo the stimulation (active: 20 minutes at 2mA, sham: 30 seconds at 2mA and then nothing). Their target quit date will be at the end of this 2 week period. They will return to the clinic every two weeks for the next 10 weeks for a booster tDCS session and to complete questionnaires. Eye tracking tests will be conducted at the end of the fourth and eighth weeks. At the end of the 12-week treatment period they will undergo a third fMRI scan and eye-tracking tests. For the next 14 weeks they will be contacted weekly by e-mail or text message to report on their smoking status as measured by the 7 day point prevalence abstinence question. “Have you had a cigarette, even a puff, in the last 7 days?” At the 6-month time point subjects will be asked to return to the clinic for a brief visit to confirm smoking abstinence using expired CO and urinary cotinine and to complete questionnaires.

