**Eye Tracking**

The eye tracking component to this study will attempt to answer several research questions. Specifically, does the magnitude of within-subject changes in VSB to smoking cues/and or emotional cues predict successful cessation and long-term abstinence? Does active tDCS change VSB to smoking cues, negative emotional cues or high-arousal/high-risk cues? Are within-subject changes in VSB to smoking/and or emotional cues correlate with the individual’s cravings? Does the individual’s VSB to high-arousal/high-risk cues correlate with long term treatment outcome? Eye movements will be recorded by Visual Attention Scanning Technology (VAST) (EL-MAR Inc. Toronto, Ontario Canada) (Guestrin and Eizenman, 2006, Pinhas et al., 2014, Chau et al., 2016) on five separate occasions (baseline, 4-weeks after start of treatment, 8-weeks after start of treatment,at the end of treatment -12-weeks and 6 months follow up). During each session, we will measure: 1) attentional bias to smoking cues, 2) attentional bias to negative emotional cues, and 3) attentional bias to high-arousal/high-risk cues.

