For the eye-tracking data, gaze position data are processed by VAST into sequences of fixations and saccades and summary statistics of visual scanning parameters are computed. The VAST parameters include: the number of fixations, the average fixation duration, the average saccadic amplitude and the number of transitions for each image type. These parameters are sensitive measures of attentional bias for different visual cues. The outcome measures of this paradigm will be analyzed using a mixed-model analysis of variance (ANOVA). The within-groups factors are the image types (smoking, neutral, high valence) and session (sessions 1, 2, 3,4 and 5) and the between-groups factor is group (active tDCS and sham tDCS). Pearson’s product–moment correlations will be conducted between parameters of attentional bias and subjective craving scores. Through analysis, we will investigate and compare the treatment effects of varenicline and active tDCS on attentional bias in different sessions. We will also examine the relationship between changes in attentional bias and craving.

By means of a mixed design repeated-measures ANOVA, the VAST parameters will be compared within-subjects at 5 sessions to investigate the effects of varenicline treatment. The parameters will also be compared between the two groups of subjects to examine the treatment effects of active tDCS. We will also compare the VSB parameters of those who quit smoking in the last 4 weeks of treatment and those who were unable to remain abstinent to find out the possible indicators of treatment outcome. Pearson correlation method will be used to explore the relationships between: a) subjective craving and VSB parameters, b) sensation seeking behavior as measured by the sensation seeking scale measures and VSB parameters. Also we will use recurrent neural networks (Chung et al, 2018) to analyze differences between fixation sequences of patients that were treated with tDCS and patients that were not, and between patients that quit smoking and those that were not. Using Cox regression of survival analysis, we will also investigate the correlation between the length of abstinence (time to relapse) and VSB parameters associated with smoking cues, negative emotional cues and high-arousal/high-risk cues.

All data analysis will be conducted using SPSS, SPM or R as appropriate.

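### Hypothesis 3 and the eye-tracking analysis attribute uncontrolled before-after change to varenicline, although both arms take it and the fifth session falls after the course has ended

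*Protocol*

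**What the plan says.** Under Design, varenicline is given in both arms: "Arm 1 will be active tDCS plus varenicline (n=25) and Arm 2 will be sham tDCS plus varenicline (n=25"). Design also has varenicline and tDCS starting together after the baseline tests, with the target quit date at the end of week 2. Pharmacological treatment sets a 12-week course.

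Hypothesis 3 reads "Compared to baseline, varenicline treatment will reduce within subject attentional bias", for smoking and negative emotional cues. Under Data Analysis (eye-tracking), the test is a mixed ANOVA with image type and "session (sessions 1, 2, 3,4 and 5") as within factors, while "the between-groups factor is group (active tDCS and sham tDCS"). The same section states that "the VAST parameters will be compared within-subjects at 5 sessions to investigate the effects of varenicline treatment".

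Eye Tracking places the five sessions at baseline, weeks 4 and 8, and then "at the end of treatment -12-weeks and 6 months follow up". Outcome Measures puts the 6-month visit at week 26.

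Background and Rationale makes a related statement for imaging, limited to one arm: "The sham tDCS group will allow us to examine the effects 12-weeks of varenicline treatment on reward anticipation in both quitters and non-quitters". It says the same of cue reactivity.

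**The concern.** A before-after change in people who all receive the same drug shows what happened while they were taking it, not what the drug did. Here several other things change between session 1 and session 2, and the protocol itself expects two of them to move the endpoint. Hypothesis 4 predicts that active tDCS lowers attentional bias and that those who quit will show normalised bias. A fall from baseline is therefore expected under the protocol's own theory even if varenicline has no effect on bias.

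The analysis text also plans to compare the treatment effects of varenicline with those of active tDCS. That sets an uncontrolled change beside a randomised contrast as though they were the same kind of evidence. At stake is a secondary finding that would be reported as confirming hypothesis 3 when the design cannot attribute it to the drug.

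**Working it through.** **Inputs, all from the Protocol.** Two arms of 25, both on varenicline (Design). Varenicline for 12 weeks (Pharmacological treatment). Eye-tracking at baseline, weeks 4, 8 and 12, and 6 months (Eye Tracking). The 6-month visit is week 26 (Outcome Measures). Quit date at the end of week 2 (Design). Self-help reading during stimulation in both arms (Procedures).

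**1. Timing.** Week 26 − week 12 = 14 weeks between the planned end of varenicline and session 5. This agrees with the 14 weeks of weekly contact given under Design. The sessions are therefore one before treatment (session 1), three on treatment (sessions 2 to 4) and one after treatment (session 5).

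**2. Comparator.** Participants randomised without varenicline: 50 − 25 − 25 = 0.

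**3. Can the drug effect be separated from session?** The group-by-session layout has 2 × 5 = 10 cells, and the full model (intercept, 4 session terms, 1 group term, 4 interaction terms) has 10 columns and rank 10. Adding a varenicline column (off at session 1, on at 2 to 4, off at 5) gives 11 columns, and the rank stays at 10. The drug indicator is an exact combination of the session terms. The model can estimate session means but cannot split them into drug and everything else.

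**4. What else changes after session 1.**
- The quit attempt at week 2, before session 2 at week 4.
- Self-help reading during stimulation.
- Elapsed time and repeated viewing of the test.
- Active tDCS in half the sample. If it shifts bias by d in the active arm and by 0 in the sham arm, the pooled change contains (25/50) × d + (25/50) × 0 = d/2 that is not due to varenicline.

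**5. Illustration under assumptions.** The document gives no SD or correlation for the eye-tracking parameters. The simulation used 25 + 25 participants, one score per session, an assumed between-session correlation of 0.5, α = 0.05, a true varenicline effect of zero, and 3,000 runs per row. The session test rejected as follows:

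| Non-drug shift in sessions 2 to 5 (SD) | Rejection rate |
|---|---|
| 0 | 4.7% |
| 0.2 | 27% |
| 0.3 | 53% |
| 0.4 | 83% |
| 0.5 | 96% |

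The score must be read as a bias score (smoking cue relative to the competing images), so the shift has to be cue-specific. On that reading, an active-tDCS effect of 0.4 SD with no other change gives a pooled shift of 0.4/2 = 0.2 SD, which is the 27% row. The table shows that a significant session effect is not evidence for varenicline. It does not estimate the bias in this trial.

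**The case against.** The best defence has several parts.

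- **Hypothesis 3 is open about its basis.** It says within subject and compared to baseline. This stands in part: the test can answer whether bias falls from baseline. A reader might infer that hypothesis 3 cannot be examined at all, but only the causal attribution fails.
- **Bias is measured against competing images on the same slide, and image type is a factor.** A shift common to all images is not a change in bias, so general practice effects are partly controlled. This stands, and it limits the simulation as described. It does not remove cue-specific changes, and quitting and active tDCS are two that the protocol predicts.
- **Quitters are compared with non-quitters.** This examines cessation but does not isolate the drug, because both groups take it.
- **Follow-up contrasts may be left to a statistical analysis plan.** This is fair for the contrasts. The protocol itself nevertheless fixes the five sessions and the varenicline reading.

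Some stronger readings are tempting but unsupported. Session is a five-level factor, so on-drug and off-drug sessions are not averaged into one mean; the difficulty is what a five-session test is taken to show. Nobody is selected on an eye-tracking score, so regression to the mean has no basis here. Research questions 2 to 4 name varenicline and tDCS together, so they do not carry the claim that hypothesis 3 makes. The imaging text limits the varenicline reading to the sham group and there is no scan after week 12, so neither the tDCS confound nor the session-5 problem applies there.

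**Conclusion.** The point holds for hypothesis 3 and the corresponding eye-tracking sentence in Data Analysis. With 0 of 50 participants off varenicline during treatment, the drug effect on attentional bias cannot be identified, and no choice of model repairs that. The missing comparator is the main fault. Two features add to it: the comparison is not limited to the sham arm, so active tDCS enters the pooled change, and one of the four post-baseline sessions is 14 weeks past the planned end of the drug.

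The direction and size of the resulting bias cannot be given from the document. The rejection rates above rest on an assumed correlation and assumed shifts.

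A reader might infer that the trial's efficacy question is compromised. It is not: active against sham tDCS is randomised, the arm-by-session-by-image-type term is already available in the stated ANOVA, and the primary outcome is untouched. This is a matter of labelling and of one contrast for a secondary outcome, worth correcting because the correction is cheap.

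**What to change.** - Reword hypothesis 3 and the eye-tracking sentence in Data Analysis as change from baseline during varenicline treatment (uncontrolled), with no causal attribution to the drug.
- Define the contrast as sessions 2 to 4 against session 1, on the image-type (bias) measure. Use the sham arm alone if the result is to be free of tDCS.
- Report session 5 separately as post-treatment follow-up.
- Give the two sham-group statements on imaging in Background and Rationale the same non-causal wording. Limiting them to the sham arm removes tDCS but not quitting, time or repeat testing.

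This needs no extra participants, visits or data. The cost is a causal claim the design cannot support. The sham-only contrast also uses 25 participants rather than 50, which for equal variance widens its standard error by √(50/25) ≈ 1.41. Reporting the pooled contrast alongside it would recover precision, provided it is stated that half the sample also had active tDCS.

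### The eye-tracking analysis names a between-group comparison as the test of tDCS without naming an interaction or adjusting for the pre-treatment session; a baseline-adjusted bias score would be better aimed and stronger at no cost

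*Protocol*

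**What the plan says.** The Data Analysis section, under the eye-tracking heading, states: "The outcome measures of this paradigm will be analyzed using a mixed-model analysis of variance (ANOVA"). It then gives the factors: "The within-groups factors are the image types (smoking, neutral, high valence) and session (sessions 1, 2, 3,4 and 5"), while "the between-groups factor is group (active tDCS and sham tDCS").

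The next paragraph assigns comparisons to questions. For varenicline, "the VAST parameters will be compared within-subjects at 5 sessions to investigate the effects of varenicline treatment". For tDCS, "The parameters will also be compared between the two groups of subjects to examine the treatment effects of active tDCS".

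Two other statements in the same section bear on how this is read. The visual scanning parameters include "the average saccadic amplitude and the number of transitions for each image type", so they exist separately by image type. And "we will investigate and compare the treatment effects of varenicline and active tDCS on attentional bias in different sessions".

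Hypothesis 4 is: "Active tDCS will reduce attentional bias to smoking and negative emotional cues compared to sham tDCS". Outcome Measures lists the eye-tracking outcome as a change in attentional bias. The Design section places the first eye-tracking test before varenicline and tDCS begin. The later ones are at weeks 4, 8 and 12 and, according to the Eye Tracking section, at 6 months.

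**The concern.** Attentional bias, as the protocol describes it, is a contrast: how a person looks at smoking images compared with neutral ones. A tDCS effect on bias is therefore an arm difference in how that contrast behaves after treatment starts. The only sentence that ties a named comparison in this ANOVA to tDCS points to the difference between groups. Session, the factor that separates before from after, is assigned to varenicline.

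A plain group comparison asks a different question: whether the arms differ in scanning overall, on average over images and over a session that no treatment can have affected. At stake is how well a key secondary outcome can answer its own hypothesis with 25 people per arm. Leaving the term unnamed also leaves several candidate tests, for several parameters and three cue sets, to be chosen after the data are seen.

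**Working it through.** The protocol gives no effect size, standard deviation or power for eye tracking, so there is no figure of its own to reproduce.

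**Inputs from the protocol.** 25 per arm (Design); five sessions, the first pre-treatment; three image types in the ANOVA; four images shown together for 10.5 s per slide (Eye-Tracking Method). Two-sided 0.05 is stated in Data Analysis for the abstinence effect and is carried over here as an assumption.

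**Assumed.** Bias score with SD 1 at each session; equal correlation ρ between any two sessions, taken as 0.4, 0.6 and 0.8; a shift of 0.5 SD at every post-baseline session and none at session 1; no dropout.

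**Step 1: the group main effect.** The ANOVA has 5 × 3 = 15 cells per arm. An effect d on smoking images at sessions 2 to 5 occupies 4 of them, so the group main effect carries (4/5) × (1/3) × d = 0.27d. If looking moves from smoking images to the others and the total does not change, the main effect is 0 whatever d is.

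A simulation (4,000 runs, 25 per arm, unit SD per cell, stable subject-by-image variance share 0.3 to 0.7) gave:

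| Scenario | Group main effect | Baseline-adjusted bias score |
|---|---|---|
| d = 0.5, smoking images only | 15–23% | 50–62% |
| d = 0.8, smoking images only | 32–50% | 88–95% |
| d = 0.5, pure redistribution | 4–5% | 83–92% |

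**Step 2: the kinder reading.** Suppose the group comparison is made on a smoking-minus-neutral bias score. The image averaging disappears and session 1 remains. With two arms of 25, the noncentrality is (effect / √variance) × √(25/2), referred to a t distribution with 48 df (47 for ANCOVA).

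- Mean of five sessions: effect 0.8 × 0.5 = 0.4; variance (1 + 4ρ)/5.
- Change from session 1 to the mean of sessions 2–5: effect 0.5; variance (1 + 3ρ)/4 + 1 − 2ρ.
- Mean of sessions 2–5 adjusted for session 1: effect 0.5; variance (1 + 3ρ)/4 − ρ².
- Mean of weeks 4, 8 and 12 adjusted for session 1: effect 0.5; variance (1 + 2ρ)/3 − ρ².

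Example at ρ = 0.6. Five-session mean: variance 3.4/5 = 0.68, noncentrality 0.4/0.825 × 3.536 = 1.71, power 39%. Weeks 4, 8 and 12 adjusted: variance 2.2/3 − 0.36 = 0.373, noncentrality 0.5/0.611 × 3.536 = 2.89, power 81%.

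| Analysis of the bias score | ρ = 0.4 | ρ = 0.6 | ρ = 0.8 |
|---|---|---|---|
| Group comparison, five-session mean | 48% | 39% | 33% |
| Sessions 2–5 mean, unadjusted | 65% | 54% | 47% |
| Change from baseline, sessions 2–5 | 52% | 69% | 93% |
| Sessions 2–5 mean, adjusted for session 1 | 79% | 84% | 96% |
| Weeks 4, 8, 12 mean, adjusted for session 1 | 74% | 81% | 95% |

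Dropping session 1 from the average gains 14 to 17 points on these figures. Using it as a covariate supplies the rest.

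**The case against.** The strongest reply is that the protocol does not say main effect. It computes parameters by image type, it declares image type and session as factors alongside group, and it intends to look at the effects of both treatments on bias in different sessions. A standard mixed ANOVA yields the interactions as well, and the exact term is often left to the SAP, which is not at hand.

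Much of this stands. A reader might infer that the protocol confines the tDCS test to the group main effect; the text does not support that. It is loosely worded. What remains is that no sentence assigns an interaction to tDCS. The one about different sessions describes an aim without a test, and a group-by-session term alone would still average over images.

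A reader might also infer that the planned test would simply miss a real effect, with power at the 5% level. That follows only if total looking is unchanged. The protocol states no such constraint, and a fixed slide time does not fix the number or duration of fixations. If only smoking-image viewing changes, power is reduced and not lost.

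Third, the gain over the five-session comparison should not be credited to the interaction. The change-from-baseline contrast gives 52% against 48% at correlation 0.4, so the larger gains there come from ANCOVA, a different and more efficient test.

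Finally, nothing in the protocol says that a non-significant result would be reported as absence of an effect on bias.

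**Conclusion.** The point holds as a free improvement. The protocol points the tDCS question at a between-group comparison, in a model whose sessions include the pre-treatment one, and names neither an interaction nor a baseline adjustment. On the least favourable reading the effect enters at 0.27 of its size, or at zero under pure redistribution. On the kinder reading of a bias-score comparison, the dilution to 0.8 and the unremoved differences between people still cost about 26, 42 and 62 points of power against the adjusted mean of weeks 4, 8 and 12 (74 − 48, 81 − 39, 95 − 33).

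These sizes rest on the assumed 0.5 SD shift, equal between-session correlations and complete data; the direction does not depend on the exact values within the range shown. The matter concerns a key secondary outcome in a 50-person pilot and does not touch the abstinence analysis. Nor is baseline adjustment foreign to the protocol: its exploratory correlations with trait factors already control session 10 scores for session 1.

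**What to change.** Replace the sentence on the between-group comparison with a definition along these lines: the effect of tDCS on attentional bias is the active-minus-sham difference in a bias score (smoking minus neutral image) over the post-baseline sessions, adjusted for the session 1 score by ANCOVA. Define a corresponding score for the negative emotional cues, whose slides carry facial expressions and so need their own contrast. State whether the 6-month session is part of the average or reported separately, since it falls after treatment has ended.

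If the ANOVA framework is kept, name the group × session × image-type contrast as the tDCS test, and recognise it as a related but less efficient alternative to the ANCOVA. The cost is wording only: the data are already to be collected and the named software can fit the model.

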**Participants**

Study participants will be 50 treatment seeking daily dependent smokers willing to make a quit attempt in the next 30 days. They will be recruited from our Nicotine Dependence Clinic and from the Greater Toronto Area through paid advertising in local newspapers and through the CAMH Registry and the CAMH website. Participants will have no concurrent Axis I psychiatric disorder (or history of substance use disorder), based on SCID, and be free of psychoactive drugs and medications, based on self-report and urinalysis. To ensure against subtle neurological deficits associated with sub-clinical alcohol misuse, men will be required to drink no more than 12 standard drinks per week and women will be required to drink no more than 9 drinks per week. These values conform to safe drinking limits for non-problem drinking (Sobell and Sobell, 1992). According to standard protocols for tDCS clinical trials, participants will also be excluded if they: a) have had recent clinically significant head trauma; b) have a history of seizures and/or epilepsy; c) are pregnant or planning to become pregnant; d) have pacemakers or implanted electrical devices such as cochlear implants; e) have metal embedded in the skull; or f) have skin lesions, open wounds, bruising, or similar injuries at either of the stimulation sites.

*Eligibility Criteria*

- Male or female
- Ages 19-65
- Daily smoker > 8 CPD
- Seeking treatment to quit smoking
- No current/recent DSM-IV Axis I diagnosis (apart from nicotine dependence)
- No current use of psychoactive drugs or medications
- No current use of Nicotine Replacement Therapy, e-cigarettes, or other medications for smoking cessation
- No history of seizures/epilepsy
- No metal embedded in the skull and/or implanted electrical devices
- No head injury (no concussion – diagnosed by a physician; OR no blow to the head with loss of consciousness for more than 1 hour)
- No known contraindications to fMRI
- No known contraindications to Varenicline
- Able to attend daily appointments for tDCS for the first 2 weeks and then once every 2 weeks for the next 10 weeks.
- Willing to undergo three fMRI scans – two at baseline and another at the end of treatment.

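### The plain Pearson correlation named for craving against attentional bias does not fix the unit of analysis and fits poorly with a within-subject question measured at five sessions

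*Protocol*

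**What the plan says.** Protocol, Hypotheses, item 4: "Subjective measures of cravings will be correlated with within-subject changes in attentional bias to smoking cues and reward anticipation". Protocol, Eye Tracking, asks the same at the level of the person: "Are within-subject changes in VSB to smoking/and or emotional cues correlate with the individual"'s cravings. Each eye-tracking test is preceded by a craving questionnaire (Free Viewing paradigm), so craving and visual scanning behaviour (VSB) are paired at every session.

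Protocol, Data Analysis, eye-tracking part, names the method twice. First, Pearson "correlations will be conducted between parameters of attentional bias and subjective craving scores". Second, "Pearson correlation method will be used to explore the relationships between: a) subjective craving and VSB parameters", with the Sensation Seeking Scale as item (b) of the same sentence. A further sentence reads "We will also examine the relationship between changes in attentional bias and craving" and attaches no method. The ANOVA in that section has image type, session and group as factors; craving is not a term in it.

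**The concern.** A Pearson correlation needs one independent pair per unit. Here each person supplies up to five pairs, and the question concerns movement within a person. The text fixes neither the unit (person or person-session) nor the quantity (level or change), and the possible choices test different null hypotheses. Some respond to stable differences between people, which could be reported as evidence that gaze bias tracks craving when it does not. Others lose most of the power that five sessions offer. At stake is the only named analysis of the craving clause in Hypothesis 4, not the treatment comparison.

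**Working it through.** **Inputs from the protocol.** 50 people ("Study participants will be 50 treatment seeking daily dependent smokers", Participants); five sessions ("session (sessions 1, 2, 3,4 and 5", Data Analysis), hence up to 50 × 5 = 250 rows. Two-sided α = 0.05 is borrowed from the effect-size paragraph of Data Analysis. No power or error rate is given for this correlation, so there is no plan figure to reproduce.

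**Assumptions.** Between-session correlation ρ of 0.4, 0.6 or 0.8, equal for craving and bias; true within-person correlation 0.3 where power is computed; between-person correlation 0 unless stated; all 50 complete all sessions. None of these is in the protocol.

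**1. Pool 250 rows.** With no link at either level, the variance of r is inflated by D = 1 + (5 − 1)ρ², and the false-positive rate is 2Φ(−1.96/√D).
- ρ = 0.4: D = 1.64, rate 12.6%
- ρ = 0.6: D = 2.44, rate 21.0%
- ρ = 0.8: D = 3.56, rate 29.9%

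Simulation agrees (about 12 to 31%). At ρ = 0.3 it gives only 8.7%.

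**2. One session, n = 50.** The correlation seen is ρ·r_between + (1 − ρ)·r_within. Power is about Φ(atanh(r)·√47 − 1.96), plus a small opposite tail.
- Within-person 0.3, between-person 0: r = 0.18, 0.12, 0.06; power 24%, 13%, 7%. Simulations range from 7 to 26%.
- Within-person 0, between-person 0.3: r = 0.12, 0.18, 0.24; rejection 13%, 24%, 39%. A positive result would not answer the within-subject question.

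**3. One change score per person (baseline to week 12), n = 50.** Differencing removes stable person effects, so the correlation seen is the within-person one.
- False positives: 4.2 to 5.8% in every simulated null without an arm effect, including between-person correlation 0.5.
- Power at r = 0.3: atanh(0.3)·√47 − 1.96 = 0.3095 × 6.856 − 1.96 = 0.16, giving 56% (simulation 55 to 58%). It is 28% at r = 0.2 and 83% at r = 0.4.
- Smallest r with 80% power: tanh((1.96 + 0.84)/√47) = 0.39; with 40 or 30 people, 0.43 or 0.49.

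*With an arm effect.* Suppose active tDCS lowers both scores by an extra d SD and there is no residual within-person link. Ignoring arm induces r = (d²/4) / [2(1 − ρ) + d²/4].
- d = 0.8, ρ = 0.6: 0.16/0.96 = 0.167, rejection 21%
- d = 0.8, ρ = 0.4: 0.16/1.36 = 0.118, rejection 13%
- d = 0.8, ρ = 0.8: 0.16/0.56 = 0.286, rejection 52%
- d = 0.5, ρ = 0.6: 0.0625/0.8625 = 0.072, rejection 8%

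**4. Within-person analysis on all five sessions.** Removing person and session means leaves (50 − 1)(5 − 1) − 1 = 195 degrees of freedom. Power at r = 0.3 is Φ(0.3095 × √194 − 1.96) = Φ(2.35) = 99%; at r = 0.2 it is about 80%. Simulated error is 4.3 to 5.4% without an arm effect.

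**5. Why session and session-by-arm are needed.** If both measures fall by 1 SD over treatment (ρ = 0.5), person-centring alone rejects 95% of the time under the null, and pooled Pearson 44%; adding session restores 5%. In the 0.8 SD arm-effect case, session alone still gives about 18%; adding session-by-arm gives about 5%.

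**The case against.** The strongest reply is that Pearson can be run on one change score per person. Hypothesis 4 speaks of within-subject changes, Data Analysis mentions changes in bias and craving, and Hypothesis 5 treats change as a person-level quantity. The plan's other regressions and correlations also use per-person summaries, such as session 10 adjusted for session 1 or changes in craving. Run that way the test keeps its 5% error rate when the arms do not differ. Nowhere does the protocol propose pooling 250 rows, and the choice of session could be left to a statistical analysis plan. The analysis is called exploratory, and the sizes above rest on a between-session correlation that the protocol does not give.

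Much of this stands. A reader might infer that the plan must be either underpowered or falsely positive, or that it intends to pool. The documents support neither: the change-score reading is open, and with 50 completers it reaches 83% power at r = 0.4.

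It does not remove the point. The two sentences that name Pearson refer to scores and parameters, while the sentence on changes names no method. The change score uses two of five sessions. It also carries no arm adjustment, although Hypothesis 4 itself predicts lower bias under active tDCS. The exploratory label lowers the stakes but does not settle which null hypothesis is tested.

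**Conclusion.** The point holds in a limited form. A within-subject question over five paired sessions is matched only with plain Pearson correlation, and the unit of analysis is not fixed. Depending on how it is run, the result has inflated error (pooled), answers a between-person question (single session), or is valid without an arm effect but inefficient (change score: about 57% power at r = 0.3, against about 99%). The change-score figure of about 21% false positives needs both an extra 0.8 SD fall in craving and in bias under active tDCS and a between-session correlation near 0.6; it moves from 13% to 52% as that correlation goes from 0.4 to 0.8. All sizes assume complete data. The protocol does not state a wrong treatment analysis, and bias by session and arm is covered by the mixed-model ANOVA. Priority is modest.

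**What to change.** In Data Analysis, eye-tracking part, replace Pearson for item (a) with a linear mixed model. The outcome is the bias score. The term of interest is person-mean-centred craving. The covariates are the person's mean craving, session, arm and session-by-arm, with a random intercept per person. State that the unit is the person-session nested in the person, and that the coefficient of centred craving answers the within-subject question. The person-mean term then reports the between-person link separately.

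Keep Pearson for item (b), the Sensation Seeking Scale, which is collected once at baseline, and say that one VSB value per person is used.

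The cost is one sentence and one model in SPSS or R, both already named in the protocol. No new data or visits are needed.
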